## Abstract

**Background:**

The very old (80+) are often described as a "frail" group that is particularly exposed to diseases and functional disability. They are at great risk of losing the ability to manage their activities of daily living independently. A health-promoting intervention programme might prevent or delay dependence in activities of daily life and the development of functional decline. Studies have shown that those who benefit most from a health-promoting and disease-preventive programme are persons with no, or discrete, activity restrictions. The three-armed study "Elderly in the risk zone" is designed to evaluate if multi-dimensional and multi-professional educational senior meetings are more effective than preventive home visits, and if it is possible to prevent or delay deterioration if an intervention is made when the persons are not so frail. In this paper the study design, the intervention and the outcome measures as well as the baseline characteristics of the study participants are presented.

**Methods/Design:**

The study is a randomised three-armed single-blind controlled trial with follow-ups 3 months, 1 and 2 years. The study group should comprise a representative sample of pre-frail 80-year old persons still living at home in two municipalities of Gothenburg. To allow for drop-outs, it was estimated that a total of about 450 persons would need to be included in the study. The participants should live in their ordinary housing and not be dependent on the municipal home help service or care. Further, they should be independent of help from another person in activities of daily living and be cognitively intact, having a score of 25 or higher as assessed with the Mini Mental State Examination (MMSE).

**Discussion:**

We believe that the design of the study, the randomisation procedure, outcome measurements and the study protocol meetings should ensure the quality of the study. Furthermore, the multi-dimensionality of the intervention, the involvement of both the professionals and the senior citizens in the planning of the intervention should have the potential to effectively target the heterogeneous needs of the elderly.

**Trial registration:**

ClinicalTrials.gov, NCT00877058

## Background

The very old are often described as a "frail" group that is particularly exposed to diseases and functional disability and who are at great risk of losing their ability to manage their activities of daily living independently [1-4]. It is a heterogeneous group, consuming a large proportion of the resources of both the health and the care and special services. It is also a group whose care, special service and rehabilitation needs vary considerably and change rapidly [5,6], requiring different professional contributions to be able to offer as adequate and appropriate intervention as possible. The ageing population is posing a challenge to the Swedish welfare system, which will increase future costs for elderly care and health care. The parliamentary bill [7]points out that research will be essential to support the development of effective and evidence-based methods of a preventive and health-promoting nature. Directing efforts for elderly men and women can lead to great gains, both health-wise and economically, both for the individual and society at large [7]. Thus, in the area of public health research, priority should be given to randomised studies evaluating the effect of such interventions in order to be able to meet the challenge posed by the growing proportion of elderly persons in the general population and the possible increasing need for health care this could generate. In this paper, we describe the design of a health-promoting and preventive intervention study directed to elderly "prefrail" people above the age of 80.

Frailty has become an established concept in research in recent years [1,8,9]. A state of decreased reserve resistance to stressors as a result of cumulative decline across multiple physiological systems is a common definition of frailty [1]. Frailty can range from mild to severe stages, and it is regarded as being strongly linked to restricted activity and morbidity. The concept [1], usually includes weakness, fatigue, weight loss, low physical activity, poor balance, slow gait speed and impaired cognition. Visual impairment is not usually included, but in recent years it has been highlighted as an important indicator of frailty, based on its impact on morbidity and disability [10-12].

The ability to manage activities of daily life deteriorates with age, and early signs such as experienced difficulties, insecurity and fatigue are often followed by the need of assistance from someone else in order to manage daily activities [13-15]. A health-promoting intervention programme could prevent and delay dependence in activities of daily life as well as the development of functional decline. Literature reviews [16-18] have examined interventions based on preventive home visits. Van Haastregt et al. [18] examined 15 trials of preventive home visits to elderly people and concluded that there was no clear evidence that preventive home visits to elderly people living in the community were effective. Stuck et al. [18]examined 18 trials, and their results indicated that home visits were effective if they were multi-dimensional and included several follow-up visits addressing "younger elderly" whose health had not yet been markedly affected. A follow-up meta-analysis [16] examining the effect of home visits to elderly (70+) persons living at home concluded that home visits reduced the disability burden among older adults if they were based on multidimensional assessment, including clinical examination. Furthermore, other studies have confirmed that those who probably benefit most from a health-promoting and preventive programme are people who have not yet suffered any restriction in activity levels or those in the early stages of activity restriction [8,19,20].

A recent review that included 14 randomised controlled studies (RCT) of multi-dimensional programs focusing specifically on frail elderly persons [21] found it difficult to conclude whether some intervention components were more successful than others, and if working in a interdisciplinary team made any difference to the outcome. The authors declared though that a multi-dimensional intervention programme targeting frail elderly persons needs diverse professionals to be able to offer a broad spectrum of intervention components to carry out an effective programme. They concluded that different professionals most likely had their own ways of "framing the problem", which implies that an interdisciplinary intervention team is desirable when dealing with the complexity of frailty. Another review [22] investigating the benefit of multidisciplinary teamwork targeting frail elderly persons living in the community concluded that our knowledge regarding the impact of multidisciplinary teams working with elderly persons is still limited.

In summary, findings from the above-mentioned studies guided the design of the health-promoting and multi-dimensional as well as multi-professional intervention named" Elderly persons in the risk zone". The study addresses very old (80+) elderly persons that are on the point of developing frailty ("pre-frail"). As the intervention is complex, both quantitative and qualitative methods were required to capture the multidimensionality of the provision and the different effects of the study. It was hoped that giving the respondents opportunities to highlight their individual priorities in their own ways might reveal ideas that had not been anticipated by the researchers, and also improve our understanding of the impact of the intervention [23]. Furthermore, the complex factors that affect the habits and ways of thinking about health and illness will be illuminated. Knowing more about how the "pre-frail" elderly persons themselves understand their health will enhance the results of the intervention study and contribute to the development of high quality care and support for this group.

### Aims and hypotheses

The authors of this intervention study aimed to prove the following two hypotheses:

1) If an intervention is made when the elderly persons are not so frail, it is possible to prevent/delay deterioration;

2) A multi-dimensional and multi-professional intervention is more effective than preventive home visits alone.

This paper presents the study design, the intervention and the outcome measures as well as the baseline characteristics of the study participants in accordance with the CONSORT recommendations for reporting pragmatic RCT [24].

## Methods/Design

### Project context

The present study was conducted in two municipalities in Gothenburg, Sweden, in which people over 80 years of age account for 8 and 7% respectively of the population, compared to Gothenburg as a whole (5%) and Sweden as a whole (5%). The aim of the municipal provision of care for the elderly is to ensure that these persons are able to live as independent lives as possible. This includes living in their own homes. When an elderly person in Sweden is no longer able to manage independently, she or he can apply for assistance from the municipal home-help services. The extent of such support is subject to an assessment of needs. The support includes meals on wheels, help with cleaning and shopping, assistance with personal care, safety alarms as well as transportation service. The elderly are also offered health care, provided either by the municipal home-help services or by the home medical care service.

### Study design

The study has an explorative, descriptive, analytical and experimental design with a follow-up for two years. The participants were randomised to three study arms: two intervention groups and one control group. Focus groups and individual in-depth interviews were conducted so that the researchers could gain an understanding of the intervention and its significance. Ethical approval was obtained for the study "Elderly persons in the risk zone" ref. no: 650-07.

### Study population

The intention was that the study group should comprise a representative sample of pre-frail 80-year old persons still living at home in two municipalities of Gothenburg. Criteria for inclusion: The participants should live in their ordinary housing and not be dependent on the municipal home help service or care. Further, they should be independent of help from another person in activities of daily living and be cognitively intact, having a score of 25 or higher as assessed with the Mini Mental State Examination (MMSE).

### Intervention

#### Intervention A; Senior meetings and one follow-up home visit

This intervention comprised 4 weekly educational senior meetings with no more than 6 participants in each group. The main purpose was to focus on two different areas, 1) information about the ageing process and its consequences, and 2) providing tools and strategies for solving the various problems that may arise in the home environment. A follow-up home visit took place about 2-3 weeks after the group had completed the group education. The group meetings were led either by an occupational therapist, a registered nurse, a physiotherapist or a qualified social worker, who jointly planned and carried out the intervention and had responsibility for their specific part of the education. A booklet especially designed for the study group was used as a basis for the meetings. The book includes texts, for example, about self-care strategies and information referring to the topics discussed at each meeting. The booklet was thus an important educational tool [25].

#### Intervention B; Preventive home visit

This intervention was in the form of a single home visit made by a nurse, a physiotherapist, a qualified social worker or an occupational therapist. During this visit the clients received verbal and written information and advice about what the municipality could provide in the form of local meeting places, activities run by local associations, physical training for seniors, walking groups etc. The clients were also informed about help and support of various kinds offered either by volunteers or by professionals employed by the municipality. They were also informed about assistive devices and adaptation of housing. Fall risks were also identified and advice on how to prevent falls were also included in the home visit. Information was also given about who they could contact for different problems.

#### Control group

This group had access to the ordinary range of services from the municipal care for the aged. If the investigator discovered that a person in the control group had any kind of need, he/she was informed about where to go for problems concerning municipal aged care.

### Research questions and outcome measurements

1. Can a health-promoting and preventive intervention for "prefrail" elderly persons:

• prevent frailty, activity limitations and morbidity,

• be a supportive factor in the social and physical environment,

• affect life satisfaction

• have an impact on the consumption of care

• be cost-effective?

2. How do the frail elderly persons experience the intervention and its importance to health?

#### Primary Outcome Measures

Frailty indicators (weakness, fatigue, weight loss, low physical activity, poor balance, slow gait speed and impaired cognition), performance of daily activities and morbidity.

#### Secondary Outcome Measures

Quality of life, life satisfaction, assistive technology, accessibility, feeling of loneliness, social interaction, social support, participatory activities, falls, fear of falling, health care consumption and mortality.

#### Measurements of frailty indicators

##### Weakness

Grip strength was measured using a North Coast dynamometer [26]. The starting position was sitting on a chair comfortably. The shoulder should be adducted and neutrally rotated. The elbow should be flexed to 90 degrees. The forearm and wrist should be in a neutral position. The dynamometer was set to mode 2, as recommended in the manual. Measurements were carried out three times per hand, with a rest in between, starting with the dominant hand. The maximum value in the dominant hand was used. In this study, reduced strength was considered to be below 13 kg for women and 21 kg for males for the right hand, and below 10 kg for women and 18 kg for males for the left hand.

##### Fatigue

The subject was asked the following question: "Have you suffered any general fatigue/tiredness over the last three months?" This question is listed under the symptoms measured with "The Göteborg quality of life instrument[27], which is a self-estimate tool giving reliable and stable measurements of symptoms. In this study those who answered yes were classified as frail.

##### Weight loss

The subject was asked the following question; "Have you suffered from any weight loss over the last three months?" This question is listed under the symptoms measured with "The Göteborg quality of life instrument (GQL) [27], which is a self-estimate tool giving reliable and stable measurements of symptoms. In this study those who answered yes were classified as frail.

##### Physical activity

This was measured with the help of a six-point scale on which the participants recorded how often they took outdoor walks. In this study 1-2 walks/week or less was considered to be reduced physical activity, and the participants who recorded this score were classified as frail.

##### Balance

This was measured with the Berg Balance Scale (BBS) [28,29] The instrument measures balance in 14 items and the assessment is made by observation. Every moment is scored using a 5-point scale (0-4). The instrument can be used on both individual and group level and has been tested for validity, reliability and sensitivity. The maximum score is 56 points. In this study, a value of 47 or lower was classified as a frailty indicator [30].

##### Gait speed

Walking four metres at a comfortable speed was taken as a measure of gait speed. If the best speed value was 0.6 metres per second or slower, this was considered to be an indicator of frailty [31].

##### Visual impairment

The KM chart [32] is a letter chart adjusted for one metre distance that measures visual acuity from 0.1-1.0. The visual acuity recorded was when 70% of the letters of the current line were correctly identified, corresponding to clinical practice. If the participant had their own glasses, they were used at the time of the examination. In this study a visual acuity of ≤ 0.5 in both eyes was classified as visual impairment.

##### Impaired cognition

This was measured with the Mini Mental State Examination (MMSE) [33]. For inclusion in the study, the participants had to be cognitively intact as assessed with a MMSE, and a cut-off of below 25 was used longitudinally to identify frailty at follow-ups.

#### Economic evaluation

The economic analysis of the intervention study will be made in the form of a cost-utility analysis (CUA), which is a variant of cost-effectiveness analysis. In a CUA the health effects of the intervention are quantified as quality-adjusted life years (QALY). The main outcome of the CUA is the incremental costs per QALY. The incremental cost utility ratio (ICUR) is calculated by comparing the difference between the intervention and the control groups in average costs per person to the difference in QALY per person. Data relating to health-related quality of life (HRQL) will be collected at baseline, 3 months, 1 and 2 years. The QALYs of the three groups will be estimated by calculating the area under the curve. Various perspectives can be taken when conducting economic analyses, such as the perspective of the hospital, primary payer or society. The perspective of this study is that of society. This implies that an attempt will be made to account for the consequences of all resource use. The costs included constitute intervention costs, and the health- and home care sector.

Table 1 gives a description of the objectives, outcome measurements and follow-ups in the study

**Table 1 T1:** Outcome measurements and follow-ups

Primary Outcome	Measurement	TO	T1	T2	T3
			3 month	1 year	2 year
Fatigue	Questionnaire/tiredness scale	X	X	X	X
Grip strength	North Coast dynamometer	X		X	X
Endurance/physical activity	Questionnaire/physical and	X	X	X	X
	activity scale	X	X	X	X
Balance	The Berg Balance Scale	X	X	X	X
Gait speed	Gait speed four-meter walking test	X	X	X	X
Weight loss	The Göteborg Quality of Life Instrument	X	X	X	X
Cognition	Mini Mental State Exam (MMSE)	X		X	X
Visual impairment	KM visual acuity chart	X		X	X
Self-rated health	SF 36 (a single question)	X	X	X	X
Illness	CIRS-G	X		X	X
Symptoms	The Göteborg Quality of Life Instrument	X	X	X	X
Depression	GDS 20	X	X	X	X
Activities of daily living	The ADL staircase	X	X	X	X

**Secondary Outcomes**	**Measurement**				

Health-related quality of life	EQ5D	X	X	X	X
Life satisfaction	Fugl-Meyer -- LiSat	X	X	X	X
Assistive technology and accessibility	Questionnaire	X	X	X	X
Participation/Leisure activities	Questionnaire	X	X	X	X
Social support	Questionnaire	X	X	X	X
Social network	Questionnaire	X		X	X
Falls	Questionnaire	X	X	X	X
Fear of falling	FES-I	X	X	X	X
Health care Consumption	Register data				

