### Statistical analysis and power calculations

The calculations will be based on the expected relative change in time, i.e. we assume that the intervention group "Senior meetings and a follow-up home visit" will change slightly or not at all in functional status; that the intervention group "Preventive home visit" will change by 15% in relation to the intervention group with Senior meetings while the "Control group" will deteriorate 20% more than the intervention group "Preventive home visit". Power calculation ensures that, if the hypotheses are true, we will be able to discover a difference of at least 15% between the intervention groups and a difference of at least 20% between the intervention groups and the control group.

Since a level of significance of alpha = 0.05 and a power of 80% are required to compare the intervention groups in a two-sided test, at least 112 persons will be required in each intervention group to be able to observe a difference of at least 15% between the groups. A comparison between the control group and the intervention groups will require 72 persons in the control group, if we assume a difference of at least 20%. A total of about 300 persons will be required.

However, to allow for drop-outs, it was estimated that a total of about 450 persons would need to be included in the study.

The analyses will be made on the basis of the intention-to-treat principle, which means that the participants will be analysed on the basis of the group to which they have been randomised [34]. Both descriptive and analytical statistics will be used to compare the groups as well as for analyses measuring changes over time. Non-parametric statistics will be used in all cases where ordinal data are analysed. Otherwise parametric statistics will be used.

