Although few drop outs are desirable, it is important to ask whether those who participated in the study are representative of the population of interest. In our study, the baseline characteristics indicated that about 80% of the participants experienced good/very good or excellent health. Nevertheless, the frailty indicators reveal that the participants experienced different degrees of frailty. Approximately 40% of the participants experienced fatigue, 60% were visually impaired, and 22-36% reported a low level of physical activity. This can be seen as evidence for the capture of the target group. However, according to statistical theories, proper randomisation should guarantee that the groups are comparable in baseline characteristics and ensure that differences between groups are due to trial effects [34]. In this study there were no statistically significant differences between the control group and the interventions groups in baseline characteristics in terms of demographic and frailty indicators, showing that randomisation was properly performed.

To enhance its quality, the study was preceded by a pilot study with the purpose of testing intervention, inclusion criteria and logistics by involving pensioners' representatives and responsible professionals in the municipality in the different phases of the planning. Meetings were held with pensioners' representatives to discuss the content and the extent of the interview. Pilot interviews were conducted in order to test the questions and the outcome measurements. Their experiences of the interview were discussed in the groups, which led to a clarification of questions and removal or substitution of outcome measurements.

Discussions were also held with the representatives about the content of the interventions and the educational material used in the interventions. The fact that the elderly themselves were involved in planning and developing the programme in close cooperation with the professionals should ensure that it will meet their needs [40]. This might mean that the intervention itself is more likely to be effective.

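### The cost-utility analysis names no adjustment of QALYs for baseline EQ5D; regressing on it would guard against chance imbalance and gain modest to large precision at almost no cost

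*Protocol article*

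**What the plan says.** The Economic evaluation section of the protocol article plans a cost-utility analysis with cost per QALY as its main result. On timing: "Data relating to health-related quality of life (HRQL) will be collected at baseline, 3 months, 1 and 2 years". Table 1 lists EQ5D under this label at all four visits, so it is taken here as the source of the utilities. On the QALY itself: "The QALYs of the three groups will be estimated by calculating the area under the curve". On the ratio: "calculated by comparing the difference between the intervention and the control groups in average costs per person to the difference in QALY per person".

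No covariate is named there. The Statistical analysis and power calculations section promises intention-to-treat analysis and says in general terms that groups will be compared. It does not mention baseline adjustment.

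The Procedure section says that the baseline interview came before randomisation. It reports 491 people randomised and 459 included: 114 control, 174 home visit and 171 senior meetings. The Discussion states: "In this study there were no statistically significant differences between the control group and the interventions groups in baseline characteristics". That sentence goes on to limit itself to demographic and frailty variables. Tables 2 and 3 do not show EQ5D.

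**The concern.** The QALY difference is the denominator of the main economic result. Taken as described, it is a difference in mean area under the curve, with baseline EQ5D used only as the first point of that area.

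People who start with higher utility tend to stay higher. If one arm happens to start higher, it will on average show more QALYs over two years with no intervention effect at all. In a ratio whose denominator may be small, a gap well within ordinary chance can change the answer noticeably, or even its sign.

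Non-significant tests on other baseline variables neither show that EQ5D was balanced nor remove a gap that is present. The variable needed to deal with this is already on the visit schedule.

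**Working it through.** The article states no QALY, EQ5D or cost-per-QALY figure, so there is nothing of its own to reproduce. The check asks how far a baseline gap carries, and how much precision adjustment would give.

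**Inputs from the article.** Visits at 0, 0.25, 1 and 2 years (Economic evaluation); 114 controls and 171 in senior meetings (Procedure).

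**Assumptions, not in the article.** Correlation ρ between any two visits equal, 0.3 to 0.7; constant variance; EQ5D standard deviation 0.20 (range 0.15 to 0.25).

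**1. Weights.** The trapezoid rule over intervals of 0.25, 0.75 and 1 year gives:
- baseline: 0.25/2 = 0.125
- 3 months: (0.25 + 0.75)/2 = 0.5
- 1 year: (0.75 + 1)/2 = 0.875
- 2 years: 1/2 = 0.5

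The sum is 2.0, and baseline holds 0.125/2.0 = 6.25% of it. The sum of squared weights is 1.28125.

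**2. Carry-over of a baseline gap d.** The expected shift in the QALY difference is d × (0.125 + 1.875ρ). The first term is the direct one; the second is persistence into follow-up.

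**3. Variance.** In units of the squared EQ5D standard deviation, Var(QALY) = 1.28125(1 − ρ) + 4ρ and Cov(QALY, baseline) = 0.125 + 1.875ρ. The share of variance removed by regression on baseline is R² = Cov²/Var. The standard error is multiplied by √(1 − R²).

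| ρ | Carry-over per unit gap | Share through persistence | Var | R² | Standard error multiplied by |
|---|---|---|---|---|---|
| 0.3 | 0.6875 | 82% | 2.097 | 0.225 | 0.88 |
| 0.5 | 1.0625 | 88% | 2.641 | 0.428 | 0.76 |
| 0.7 | 1.4375 | 91% | 3.184 | 0.649 | 0.59 |

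If correlation instead decays with distance between visits (one, two and three visits apart), 0.5/0.4/0.3 gives 30% of variance removed and 0.7/0.6/0.5 gives 51%.

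**4. Size in QALYs, senior meetings versus control.** The standard error of the baseline gap is 0.20 × √(1/114 + 1/171) = 0.024. A gap of 1.96 standard errors carries 1.96 × 0.0242 × 0.6875 = 0.033 QALY at ρ = 0.3, 0.050 at 0.5 and 0.068 at 0.7. These figures scale with the standard deviation: at ρ = 0.5, 0.15 gives 0.038 and 0.25 gives 0.063. With 0.20, adjustment lowers the standard error of the QALY difference from 0.035 to 0.031 (ρ = 0.3), 0.039 to 0.030 (0.5) and 0.043 to 0.026 (0.7).

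**5. Why regress rather than subtract.** Subtracting 2 × baseline from each QALY gives variance Var − 4Cov + 4. Relative to the unadjusted variance this is 3.347/2.097 = 1.60 at ρ = 0.3, 0.91 at 0.5 and 0.45 at 0.7. Regression gives 0.77, 0.57 and 0.35. Subtraction can therefore make matters worse, and regression is better at each value.

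**6. Losses after randomisation.** Control 0 of 114; home visit 4 of 178 (2%); senior meetings 23 + 5 = 28 of 199 (14%), including 5 who fell ill. The total is 32 = 491 − 459. If the economic analysis is run on the 459, a baseline gap need not be due to chance alone.

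**The case against.** The strongest reply is that the article never calls the difference unadjusted. Its two sentences define the QALY and the ratio, and both would remain true if the difference came from a regression. A full analysis plan, not shown, may already adjust. This stands: a reader might infer that the plan prescribes a raw difference and rules out a covariate, but the text supports only that no adjustment is named. The point is therefore put as an improvement to a described calculation, not as an error or an omission.

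Three other stronger readings also fail:
- **Bias.** One might infer that the QALY comparison is biased. Under intact randomisation it is not, and its standard error already allows for chance imbalance. A systematic gap is only a possibility, conditional on analysing the 459.
- **The baseline term.** One might blame the inclusion of baseline in the area. That term carries 6.25% of the weight, and dropping it would leave most of the carry-over in place.
- **Imbalance observed.** No EQ5D by arm is reported. The nearest item, self-rated health in Table 2, is 79%, 80% and 83% (p = 0.63). The Discussion's statement on baseline tests concerns other variables and is not offered as a reason to leave QALYs unadjusted.

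It is also fair that the size rests on assumed correlations. Mortality is a listed outcome. If deaths are scored as zero utility, constant variance and equal correlation need not hold, and the gain could fall outside the range shown.

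**Conclusion.** The point holds as a low-cost improvement to the secondary economic analysis. As described, the denominator of the ratio is a difference in mean QALYs with no named adjustment for a pre-randomisation measure that is scheduled in all arms. The costs are exposure to chance imbalance in baseline utility and lost precision, with a possible systematic gap if the unequal losses are carried into the analysis.

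Under equal correlation of 0.3 to 0.7, adjustment removes about 23% to 65% of the variance (standard error 12% to 41% lower). That is a modest to large gain; the article gives no figure that would settle where in the range it falls. The QALY amounts depend further on the assumed EQ5D standard deviation. Nothing here touches the primary outcomes or the sample size.

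**What to change.** In the Economic evaluation section, or in the analysis plan if one exists, add a statement along these lines:

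> Each participant's 2-year area-under-the-curve QALY will be regressed on study arm with baseline EQ5D utility as a covariate. The adjusted arm difference will be the denominator of the cost-utility ratio. The unadjusted difference will be reported as a sensitivity analysis.

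Use regression, not subtraction of baseline. If a full plan already does this, a cross-reference is enough.

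The cost is one sentence and one regression, with no new data. A participant with missing baseline EQ5D needs imputation, but the area under the curve already needs that value. The adjustment deals only with the part of any loss-related gap that baseline EQ5D captures. It does not replace analysing everyone as randomised, which the article already promises.
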